### Withdrawal of trial participants

Participants can withdraw from the trial at any time for any reason without their medical care being affected. Data already collected will continue to be used, and the patients will be asked if they are still willing to provide follow-up data. The reason for withdrawal will be documented whenever possible.

### Statistical methods

Absolute values of continuous variables will be expressed using standard summary statistics, arithmetic mean, standard deviation, and corresponding 95 % confidence interval. The study is designed to compare recurrence rates of AF or atrial tachycardia episodes at 24 months between two treatment groups as the primary endpoint. The arrhythmia-free survival rate is defined as the percentage of patients free of atrial arrhythmias. Fisher’s exact test will be used for this categorical data to assess the difference in frequency of arrhythmia recurrence. The odds ratio and its 95 % confidence interval will be estimated as a quantitative measure of risk in the association frequency table. Differences in continuous data describing duration of arrhythmia recurrences will be tested using Student’s *t* test. Kaplan-Meier curves will be plotted to compare event-free survival time between both groups. The log-rank test will be performed to compare arrhythmia-free survival time distributions between the study arms. Influence of mutually independent risk factors will be quantified on the basis of the hazard ratio (HR) and its 95 % confidence interval. Both univariate and multivariate adjusted HRs will be estimated using the Cox proportional hazard models with an adopted forward stepwise algorithm. All variables will be analyzed on the basis of the intention-to-treat protocol. A *P* value less than 0.05 will be considered as a boundary of statistical significance of differences in all performed tests. Analyses will be performed using SPSS version 16.0 (SPSS Inc., Chicago, IL, USA).

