## Background

Atrial fibrillation (AF), the most common clinically significant cardiac arrhythmia, is associated with increased mortality and morbidity [1]. The incidence of AF will continue to increase due to aging of the population. In patients indicated for cardiac surgery, the prevalence of AF is higher compared to the general population [2], and it can be as high as 50 % in individuals with mitral valve disease [3].

Both surgical and catheter ablation have become recognized treatments for symptomatic and drug-refractory AF. The CryoMaze ablation procedure was developed as a surgical alternative to cut-and-sew procedures as a way to decrease invasiveness [4]. A variety of surgical ablation energy sources have been used including microwaves, laser, and unipolar or bipolar radiofrequency energy. The CryoMaze operation is usually done in conjunction with a coronary bypass operation, valve surgery, or other open heart surgery. Incomplete lines after surgical ablation are common and can be pro-arrhythmic [5, 6]. The efficacy of the CryoMaze procedure as the sole treatment for persistent AF has been shown in several studies, but the results are hindered by small patient numbers and less than accurate follow-up assessments of heart rhythm, such as via telephone interviews with only occasional use of continuous electrocardiographic (ECG) recordings [4, 7]. This has led to mixed results, with rates of freedom from AF being reported between 47–95 % [8, 9]. Additionally, the need for subsequent transvenous catheter procedures remains unknown; also, the clinical procedures employed varied between centers.

In a non-randomized study, sequential surgical CryoMaze procedures followed by catheter ablation led to high freedom from arrhythmia in patients with persistent and long-standing persistent AF and without an increase in complications [10]. However, there have been no randomized clinical trials conducted to evaluate whether the hybrid approach is superior to a CryoMaze procedure alone; therefore, a recommendation regarding the best procedure for all patients is unavailable.

The aim of this randomized, multicenter clinical trial is to compare clinical efficacy and safety of the staged hybrid ablation to a CryoMaze procedure alone in a well-described population of patients with AF.

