### Randomization

The SurHyb study is a prospective, randomized, multicenter study. After providing informed consent, patients will be randomly assigned using a computer system to one of the two groups — the hybrid group or the surgery alone group — initially in a 1:1 ratio. The surgeon will be blinded as to the treatment group until the surgery is completed. All patient data will be collected using a standard form and transmitted to a central database.

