### Primary outcome measure

The primary outcome measure is arrhythmia-free survival without class I or III antiarrhythmic drugs, which will be evaluated using a 7-day Holter monitoring at 24 months. After a 3-month blanking period, if a patient requires a repeat ablation, cardioversion, or antiarrhythmic drugs, this will be considered as a failure.

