### Secondary outcome measures

The secondary outcome measures involve arrhythmia-free survival without class I or III antiarrhythmic drugs and without a need for repeat ablation or cardioversion, evaluated using a 7-day Holter monitoring at 6, 12, and 18 months. The measures include:Arrhythmia-free survival regardless of antiarrhythmic drugs status or re-do ablationsNumber of cardioversionsNumber of re-do ablationsFrequency and duration of hospital admissions for recurrent arrhythmiasFrequency and description of any procedure-related complications (during both surgical and catheter ablation)Cardiovascular mortality and morbidityChanges of left atrial dimension as measured using ultrasound echocardiography

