### Sample size calculation

Power calculations to provide estimates for the necessary sample size were conducted concerning recurrence rates of AF or atrial tachycardia episodes at 24 months as the primary outcome endpoint. The clinical efficacy of the hybrid ablation procedure was assumed to be 86 %, whereas the efficacy of the surgical ablation alone was assumed to be 50–70 %. To ensure 80 % power of the Fisher exact test at the 5 % significance level, a sample size of at least 130 must be included in each of the trial arms. Considering a dropout rate of 20 %, approximately 170 patients will finally be recruited for each trial arm. At the end of the study, the number of patients free from arrhythmias should be similar in both groups, but the proportion of those submitted to another procedure, commenced on antiarrhythmic drugs, or undergoing cardioversion should differ significantly.

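### The P < 0.05 rule for all tests lets any of about 8 to 12 unordered secondary comparisons be called statistically significant even if the 24-month primary fails

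*Protocol article*

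**What the plan says.** The article names a single primary outcome. Under Primary outcome measure it states: "The primary outcome measure is arrhythmia-free survival without class I or III antiarrhythmic drugs", assessed at 24 months, with repeat ablation, cardioversion or antiarrhythmic drugs after blanking counted as failure. The sample size rests on this endpoint alone: "To ensure 80 % power of the Fisher exact test at the 5 % significance level".

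Secondary outcome measures begins with the same arrhythmia-free, drug-free composite "evaluated using a 7-day Holter monitoring at 6, 12, and 18 months". It then adds:
- arrhythmia-free survival ignoring drugs and re-do procedures;
- counts of cardioversions and of re-do ablations;
- how often and how long patients are admitted for arrhythmia;
- procedural complications;
- cardiovascular death and morbidity;
- change in left atrial size.

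The list has no ranking, no condition on the primary result and no exploratory label.

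Statistical methods then gives one decision rule for everything: a *P* "value less than 0.05 will be considered as a boundary of statistical significance of differences in all performed tests". Whether tests are one- or two-sided is not stated.

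**The concern.** The article does more than leave multiplicity open. It states a rule, and the rule covers every test performed. Under it, a secondary *P* value of 0.04 has the same formal status as a primary *P* value of 0.04, whether or not the primary was significant.

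The 6-, 12- and 18-month outcomes matter most. They use the primary's own definition at earlier visits, so they are obvious substitutes if the 24-month comparison misses. The aim in Background is broad (to "compare clinical efficacy and safety of the staged hybrid ablation to a CryoMaze procedure alone"), so a significant secondary could be presented as answering it.

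The last sentence of Sample size calculation also expects the proportions needing another procedure, antiarrhythmic drugs or cardioversion to differ significantly. Re-do ablations and cardioversions are on the secondary list. They are also components of primary failure, so that sentence may describe the composite. Even so, it makes it harder to assume that the secondaries are tacitly exploratory.

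At stake is whether the report could announce a statistically significant advantage of hybrid ablation on a secondary outcome with no protection against chance findings across the list.

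**Working it through.** **The plan's own figure.** There is none to reproduce. The article gives a per-test threshold of 0.05 and no error rate for the secondary family.

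**Count of comparisons (k), from Secondary outcome measures.**
- Splitting the two-part items: 3 (composite at 6, 12, 18 months) + 1 (regardless of drugs or re-do) + 1 (cardioversions) + 1 (re-do ablations) + 2 (admission frequency, admission duration) + 1 (complications) + 2 (cardiovascular mortality, morbidity) + 1 (left atrial dimension) = 12.
- Taking admissions as one item and treating complications and cardiovascular mortality and morbidity as descriptive: 3 + 1 + 1 + 1 + 1 + 1 = 8.

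**Assumptions.** Every counted outcome is tested two-sided at 0.05, there is no true difference on any of them, and the test statistics are normal with a common correlation ρ. The article gives no correlation, so a range is shown.

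**Independent tests.** Chance of at least one false significant result = 1 − 0.95^k.
- k = 8: 1 − 0.95^8 = 0.337
- k = 12: 1 − 0.95^12 = 0.460

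**Correlated tests, either direction.** 1 − ∫ [Φ((1.96 − √ρ·x)/√(1−ρ)) − Φ((−1.96 − √ρ·x)/√(1−ρ))]^k φ(x) dx.

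**False benefit of hybrid ablation only.** 1 − ∫ [Φ((1.96 − √ρ·x)/√(1−ρ))]^k φ(x) dx. At ρ = 0 this is 1 − 0.975^k, that is 0.183 for k = 8 and 0.262 for k = 12.

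| Tests | Direction | ρ = 0 | ρ = 0.3 | ρ = 0.5 | ρ = 0.8 |
|---|---|---|---|---|---|
| 8 | either | 0.34 | 0.30 | 0.25 | 0.16 |
| 12 | either | 0.46 | 0.40 | 0.32 | 0.19 |
| 8 | false benefit | 0.18 | 0.15 | 0.13 | 0.08 |
| 12 | false benefit | 0.26 | 0.20 | 0.16 | 0.09 |
| 3 (6, 12, 18 months) | either | 0.14 | 0.14 | 0.13 | 0.10 |
| 3 (6, 12, 18 months) | false benefit | 0.07 | 0.07 | 0.06 | 0.05 |

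For comparison, a single two-sided test at 0.05 has a 0.025 chance of a false benefit. None of these figures is conditional on the primary having failed.

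**Effect of conservative exact tests.** With 130 per arm, enumeration gives an actual two-sided size for Fisher's test of about 0.009 at a 2 % event rate, 0.022 at 5 % and 0.036 at 22–30 % (assumed rates). If every test had size 0.036, the independent figures would fall to 1 − 0.964^8 = 0.25 and 1 − 0.964^12 = 0.36. At ρ = 0.8 the same integral, with 1.96 replaced by 2.10, gives 0.12 and 0.14.

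**The case against.** The strongest reply is that this is a condensed article with an analysis plan that may exist elsewhere. Ordering or labelling of secondary outcomes is commonly left to that plan, and a sentence giving a nominal threshold is conventional. The hierarchy that matters is present: one primary outcome, the sample size built on it, and everything else called secondary. This stands in part. Missing adjustment alone would not be a finding. But the article states a rule for all tests, and an analysis plan that controlled multiplicity would have to override it.

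The second reply is that the number of tests is assumed. Statistical methods assigns tests to arrhythmia recurrence, to duration of recurrences and to event-free survival. It assigns none to cardioversions, re-do ablations, admissions, complications, mortality and morbidity, or left atrial size. Complications are to be described as well as counted. They are also a poor member of a false-benefit family, since only the hybrid arm has a planned second procedure. This stands, so the figures are conditional on testing and span 8 to 12 comparisons.

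The third reply concerns size. A reader might quote a single figure such as 32 %. That needs 12 tests and an assumed correlation of 0.5, counts errors in both directions and gives every test its full 0.05. For the most tempting substitutes, the three earlier visits, the chance of a false benefit is only about 5 % at a correlation of 0.8. This also stands.

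Two stronger readings are not supported. The article does not declare any secondary outcome significant; it sets a threshold. Nor is the primary's error rate inflated by these tests, because the 24-month comparison is separate from them.

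**Conclusion.** The concern holds, with modest weight. The rule as written allows a statistical-significance claim on any secondary outcome, including the primary composite at 6, 12 or 18 months, even if the 24-month primary fails.

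If all secondaries are tested, the chance of at least one false significant difference in either direction is about 16–34 % for 8 tests and 19–46 % for 12. The ranges run from a common correlation of 0.8 to 0. Positive correlation is plausible, because the outcomes include repeated rhythm assessments and the procedures that follow from them, so the independent figures are best read as upper ones. The false-benefit figures are about half (8–13 % and 9–16 % at correlations of 0.8 to 0.5), and conservative exact tests lower all of them. The conclusion depends on the stated rule, not on any one of these numbers. The primary's 5 % error is unaffected.

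**What to change.** Restate the closing rule in Statistical methods along these lines: *P* < 0.05 defines statistical significance for the 24-month primary endpoint only; secondary outcomes are exploratory and are reported as estimates with 95 % confidence intervals, without claims of significance. Report complications and mortality descriptively with confidence intervals, so that no safety signal depends on a significance threshold.

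If the sponsor wants confirmatory secondary claims, pre-specify a short fixed sequence, tested only if the primary is significant, each step at 0.05 and stopping at the first failure. One example is the drug-free composite at 18, then 12, then 6 months. All other secondaries stay exploratory.

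The cost is one or two sentences before database lock, with no extra patients, data or procedures and no loss of power for the primary. The downside is that a secondary with *P* < 0.05 outside the sequence can no longer be called statistically significant.

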### Sample size calculation

Power calculations to provide estimates for the necessary sample size were conducted concerning recurrence rates of AF or atrial tachycardia episodes at 24 months as the primary outcome endpoint. The clinical efficacy of the hybrid ablation procedure was assumed to be 86 %, whereas the efficacy of the surgical ablation alone was assumed to be 50–70 %. To ensure 80 % power of the Fisher exact test at the 5 % significance level, a sample size of at least 130 must be included in each of the trial arms. Considering a dropout rate of 20 %, approximately 170 patients will finally be recruited for each trial arm. At the end of the study, the number of patients free from arrhythmias should be similar in both groups, but the proportion of those submitted to another procedure, commenced on antiarrhythmic drugs, or undergoing cardioversion should differ significantly.

### Data management

A tailor-made website has been developed for the SurHyb study. Each participating medical center will have access to a dedicated part of the website. After enrollment and randomization of participants, data from medical records, drug regimens, interviews, and electrocardiograms will be added to the website. The website will be updated after each outpatient clinical visit during the follow-up period. The follow-up status of all patients can be viewed instantly.

At the end of the study, all data will be entered and stored on a password-protected computer. A data monitoring committee, of which at least two members will be independent of the research team, will monitor the data management process regularly. All data will be frozen and locked to prevent further editing after validation by the data monitoring committee. Only the data monitoring committee, the study research assistant, and the principal investigator will have access to the final data set. This committee will meet twice per year. Using statistical criteria for acceptable deviations from the null hypothesis, the committee will advise whether the recruitment can continue or whether the study should be terminated. The final analysis will be performed after all the patients complete their 2-year follow-up.

Reasons for dropouts and the number of patients in each group will be reported. This information will be used to see how missing data will be handled in statistical analysis. Data already collected will continue to be used and, if possible, post-dropout data will be collected on the main endpoints. In case of a high percentage of missing data, imputation techniques might be required.

### Safety monitoring

The local investigator at each site will review safety data for the duration of the trial. Serious adverse events are defined as life-threatening events or events resulting in death or hospitalization. All serious adverse events linked with the study will be reported to the Budweis Hospital research ethics committee within 24 hours of study staff becoming aware of the event and in accordance with the institutional research ethics committee requirements. Serious adverse events will be completed with detailed information, such as event description, date of onset and resolution, severity, and action taken.

## Discussion

This randomized controlled trial is the first of its kind in which hybrid ablation will be compared with surgical CryoMaze alone to compare differences relative to freedom from atrial tachyarrhythmia.

CryoMaze ablation is a less invasive modification of the original cut-and-sew method using a cryoprobe to create ablation lesions. Success rates have been reported to be as high as 95 % at 12 months; however, follow-ups were conducted through telephone interviews only [4]. When more accurate methods to determine heart rhythm were used, such as ECG Holter monitors over several days, success rates fell to 76 % at 12 months [9]. Other authors have reported less promising outcomes. In one study, only 47 % of patients with persistent AF who underwent surgical CryoMaze with concomitant cardiac surgery were in long-term normal sinus rhythm [8].

Hybrid ablations may overcome the limitations associated with both surgical and transvenous endocardial ablations alone. Neither of the approaches alone can guarantee complete transmurality, which is crucial, particularly with regard to persistent AF requiring relatively long continuous lesions. It is also possible to ablate arrhythmia triggers and inducible atrial tachycardias after the surgical ablation; these would otherwise be left untreated. Studies published to date included simultaneous or sequential hybrid procedures with reported success rates from 83–94 %, but the experience has only been with bipolar or monopolar radiofrequency energy [12–15]. The only report on hybrid ablations with cryoenergy used during the surgical part of the procedure revealed an overall freedom from atrial tachyarrhythmias to be 86 % at 12 months. The overall success rate at 1 year can reach 94 % if patients on antiarrhythmic drugs or patients who underwent a successful re-do ablation are not excluded as a failure [10]. There is certainly reporting bias among published studies, as several large studies of hybrid AF ablation, including the staged Dual Epicardial Endocardial Persistent (DEEP) AF study, FAST-II, and SCALA have not yet been published.

Data from randomized trials comparing hybrid ablations to either surgical or catheter ablation are lacking, but several randomized clinical trials are ongoing. The staged transthoracic approach to persistent AF (TOP-AF) study is a randomized controlled trial comparing percutaneous catheter ablation with surgical ablation as the first procedure followed by a second procedure, if necessary [16]. The researchers anticipate that the use of a staged strategy combining surgical and percutaneous approaches might be more favorable in treatment of persistent AF than a single percutaneous ablation. Another ongoing trial (Prospective, Randomized Comparison of Hybrid Ablation vs. Catheter Ablation, PRHACA) will compare endocardial catheter ablation using the Arctic Front CryoAblation catheter (Medtronic, Minneapolis, MN, USA) to isolate the pulmonary veins and a Navistar Smart Touch catheter (Biosense Webster, Diamond Bar, CA, USA) to create ablation lines during the hybrid surgical ablation using a VisiTrax ablation device (nContact, Morrisville, NC, USA) for the surgical portion of the procedure. As far as we know, there are no ongoing randomized trials using cryoenergy for the surgical part of the hybrid procedure.

## Trial status

The trial is currently in the recruitment phase.

## Abbreviations

AF: Atrial fibrillation
E/A ratio: Early to late diastolic filling ratio
ECG: Electrocardiographic
PRHACA Prospective: Randomized Comparison of Hybrid Ablation vs. Catheter Ablation
